###### Neurological Evaluation

Detailed patient history and clinical neurological examination will be performed. The symptoms and findings relevant for polyneuropathy and neuropathic pain will be scored according to the Toronto Neuropathy Symptom Score, Douleur Neuropathique 4, and Neupsig criteria for neuropathic pain [61-63]. Standard nerve conduction studies on three motor nerves (ulnar, peroneal, and tibial), four sensory nerves (ulnar, radial, superficial peroneal, and sural), and one mixed motor or sensory nerve (tibial plantar nerve) will be performed. Assessment of small fiber function will be conducted by quantitative thermal testing (cold perception threshold and warmth perception threshold) on the hands and feet. All measurements will be performed on the right extremities. The temperature will be maintained at >30 °C in feet and >32 °C in hand. Polyneuropathy will be diagnosed and classified according to the criteria suggested by Tesfaye et al [64] as possible, probable, or confirmed polyneuropathy (clinical grading) and according to the Tesfaye neurophysiological criteria (stadium 0, 1a, 1b, 2a, and 2b), which includes subclinical polyneuropathy.

###### Anthropometry and Maturity

Body weight will be measured using a digital scale (SECA 876 GmbH and Co), with participants wearing light clothing and no shoes. Height will be measured using a stadiometer (SECA 217 GmbH and Co). Body composition will be assessed by dual-energy x-ray absorptiometry (Lunar iDXA GE Healthcare using the enCORE software Version 14.10.022). Participants will be scanned from head to toe in a supine position, providing values for total lean tissue (kg), fat mass (kg), bone mineral content, and bone mineral density. In WP 2, the puberty stage of survivors of childhood cancer will be assessed clinically by a medical physician at the first visit in Norway. In addition, all participants (survivor of childhood cancer and controls) will self-assess their puberty stage using a modified Tanner method [65].

###### Muscle Thickness

Muscle thickness and pennation angle of the musculus vastus lateralis and thickness of the musculus biceps brachii will be measured by B-mode ultrasound using a linear-array transducer (50 mm, 5-12 MHz, HD11XE, Philips Ultrasound, revision 2.0.3). The sites for the measurements will be on one-third of the humerus length measured from the lateral epicondyle for the musculus biceps brachii and on 40% of the femur length measured from the lateral epicondyle for the musculus vastus lateralis.

###### PA Measures

Whenever the time between participation in WP 1 and recruitment in WP 2 exceeds 3 months, PA will be remeasured by accelerometers as described above (WP 1).

##### Data Management

Study data will be collected and managed using REDCap (Research Electronic Data Capture) electronic data capture tools hosted at the Norwegian School of Sport Sciences [66,67]. REDCap is a secure, web-based software platform designed to support data capture for research studies. Data from all sites will be entered by the study sites independently in REDCap.

##### Power Calculation and Statistical Analyses WP 2

Sample size calculations and power assessment were based on VO_2_peak. On the basis of results from international studies, we expect to find a difference of 10% between survivors of childhood cancer and controls [22]. To detect a difference of 10% in VO_2_peak between survivors and healthy controls, with a statistical strength of 80%, the study needs to include 23 survivors of childhood cancer. The same number of patients are needed to get the same statistical power for the strength tests assuming a difference of 10%. Owing to heterogeneity between diagnostic groups and the need for subgroup analysis (diagnosis, age, and gender), we plan to include 150 survivors as we expect the group size to be as small as 30 participants.

We will use descriptive statistics to present the current PF, physiological determinants of PF, and PA of survivors of childhood cancer compared with controls. We will use multilevel (mixed) linear models to compare PF and PA between survivors of childhood cancer and controls and include an interaction term (for instance, age group, gender, and diagnosis) to identify differences in physiological determinants between survivors of childhood cancer and controls. All analyses will be adjusted for the study site by including sites as random intercepts in the mixed models. Where available and depending on the research question, the fitness outcomes will be transformed into *z* scores according to the norm data. Depending on the outcome, we will perform univariable and multivariable mixed logistic, linear, or ordinal regression models to identify clinical and physiological factors associated with PF in survivors.

#### WP 3

The outcomes of WP 3 include facilitators of and barriers to PA. Norway (Oslo and Bergen) and Denmark (Copenhagen) will participate in WP 3.

##### Theoretical Framework and Procedures

The World Health Organization’s International Classification of Functioning, Disability, and Health for Children and Youth (ICF-CY) illustrates the interrelationships between body functions and structural impairments (eg, late effects), activity limitations, and restricted ability to participate within an individual’s context of environmental and personal factors to predict outcomes (eg, functioning and health) [68]. Therefore, the ICF-CY is a suitable biopsychosocial framework to systematically identify potential barriers to and facilitators of PA among young survivors of childhood cancer. Inspired by the ICF-CY model, we will explore facilitators of and barriers to PA through in-depth interviews with young survivors of childhood cancer and their parents. A semistructured interview guide will be developed based on current knowledge of barriers to and facilitators of PA and inspired by the ICF-CY framework (Multimedia Appendix 1) to be used at all 3 sites. The interviews will follow the guide and last approximately 15 to 60 minutes. All interviews will be audio recorded and transcribed ad verbatim.

##### Data Analysis WP 3

NVivo software will be used for data management and analysis [69]. Analysis will be conducted in parallel with data collection to ensure that any new issues of interest arising are explored in subsequent interviews. Interviews from survivors and parents will be analyzed separately. All data will be analyzed according to the principles of thematic analysis [70,71]. After familiarization with the initial interviews, at least two researchers will analyze the data line by line, creating codes reflecting the contents of each utterance to ensure objectivity [72,73]. Any disagreements regarding the codes will be discussed with the project group and settled. For analytical rigor, codes will be used and discussed by all members of the research team to develop a codebook that will be used in all interviews for all sites. We will follow the COREQ (Consolidated Criteria for Reporting Qualitative Studies) guidelines for conducting and reporting qualitative research [74].

#### WP 4

##### Overview

WP 4 aims to develop and feasibility test a sustainable and safe PA intervention for survivors of childhood cancer based on the results obtained in WPs 1 to 3. Norway, Finland, and Germany will participate in WP 4. The study will comprise two study visits (baseline and after 6 months), including self-reported questionnaires, interviews, measurement of PA, and PF tests (Table 1; Table S1 in Multimedia Appendix 1). In between, the survivors will participate in a personalized PA intervention, followed by central and local coaches.

In specific, we aim to do the following:

Describe the adherence to and acceptability, satisfaction, and safety of the personalized PA interventionTest the involvement of local structures (parents, school, teachers, peers, community and school nurses, and sports clubs) to improve the PA of survivorsAssess the effect of the intervention on PA, attitude toward PA, QoL, fatigue, and PFExplore the experiences of survivors of childhood cancer and their parents of participating in the PA interventionExplore the central coaches’ experiences providing the intervention and collaborating with local structures

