## Methods

### Study Design, Study Population, and Inclusion Criteria

The PACCS study [33] is an international multicenter study based on a mixed methods design that combines clinical and physiological assessment methods, patient-reported outcome measures, qualitative interviews, and a feasibility intervention. WPs 1, 2, and 3 have a cross-sectional design, whereas WP 4 will be a single-arm (intervention only), multicenter, open PA feasibility trial. The study population comprises young survivors of childhood cancer (aged 9-18 years) recruited from seven medical centers in Europe: 2 in Norway (Oslo and Bergen) and Finland (Turku and Tampere) and 1 in Denmark (Copenhagen), Germany (Essen), and Switzerland (Basel). Survivors of childhood cancer with *any* malignant disease, at least 1 year after completion of cancer treatment, and those attending outpatient follow-up care consultations are eligible for inclusion. Survivors of childhood cancer will be excluded if there are language difficulties or limited cognitive functioning. Figure 1 provides an overview of the different WPs.

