##### Assessment of PA and Sedentary Time by Accelerometer

PA and sedentary time will be assessed objectively by accelerometers worn for 7 days during the awake time to measure accelerations of +6 G to –6 G (ActiGraph model GT3X+, ActiGraph LLC). The sample rate of the accelerometer is set to measure the raw signals at 30 Hz. Total PA will be described as the number of counts per minute (cpm), which is a measure of the volume of PA assessed by the accelerometer. The accelerometer data will be uploaded by all collaborators to a central server located at the Norwegian School of Sport Sciences and analyzed at one site. Accelerometer measurements with at least four valid measurement days (≥480 min/day) will be included in the analysis.

The activity counts from the accelerometers will be translated into metabolic energy equivalents of intensities as sedentary time (<100 cpm), light (100-1999 cpm), moderate (2000-5999 cpm), and vigorous (>6000 cpm) PA [42]. Participants will be categorized as reaching the international recommendations for PA if they engage in at least 60 minutes of moderate to vigorous PA (≥2000 cpm) per day on average over valid accelerometer measurement days.

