###### PA Parameters

PA will be measured by an accelerometer as described for WP 1 at baseline and after 6 months. In addition, the PA will be tracked continuously with the Polar watch (Polar Global). At each follow-up discussion with the central coaches, the survivors will be asked about their participation in the agreed PA program and, if applicable, reasons for nonparticipation.

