## Results

Research activity for this study commenced in November 2016 with the piloting of questionnaires and recruitment to WP 1 at the Oslo, Norway site. The project received funding from the Research Council of Norway for the period from June 2018 to June 2022. International collaboration was established after June 2018. Data collection at all sites was initiated by October 2020 for WP 1 and concluded on January 2021, with 517 survivors of childhood cancer included. Data cleaning and analysis are currently underway. A total of articles are under preparation for publication. Data collection for WP 2 was initiated in January 2019 and concluded in December 2020, with 157 survivors of childhood cancer and 113 controls included. Data cleaning and analysis are currently being conducted. A total of 6 articles are planned based on the WP 2 data set. Data collection for WP 3 was initiated in January 2018. Patient and parent interviews were concluded in July 2020, with 63 survivors of childhood cancer and 68 parents. Interviews with local stakeholders were initiated in January 2020 and concluded in October 2020, with a total of 18 participants interviewed (teachers, special needs teachers, and school nurses). Data from the patient and parent interviews have been analyzed and are currently being written for publication. A total of 2 articles have been published as of January 2022 [81,82], and 2 more are under preparation for publication. Data from interviews with local stakeholders are currently being analyzed, and 1 article is planned. WP 4 recruitment was initiated in May 2021 and is still ongoing as of January 2022. The study is planned to be completed by July 2022. As of January 2022, 23 survivors of childhood cancer have been included, of which 11 have completed the intervention. Detailed plans for data analyses for WPs 1 to 4 are described in the "Assessments, Power Calculations, and Statistical Analyses" section.

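### WP 4 sets out to assess an intervention effect, but its single-arm change over about 6 months cannot be separated from season (for PA) or growth (for raw fitness)

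*Protocol article*

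**What the plan says.** The WP 4 Overview lists five aims. Four concern adherence, acceptability and safety, the involvement of local structures, and the experiences of families and coaches. The remaining one is to assess "the effect of the intervention on PA, attitude toward PA, QoL, fatigue" and PF.

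The design and measurement schedule for that aim are:

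- **Arms.** Under Study Design, Study Population, and Inclusion Criteria: "WP 4 will be a single-arm (intervention only), multicenter, open PA feasibility trial".
- **Visits.** In the WP 4 Overview: "The study will comprise two study visits (baseline and after 6 months". No visit window is given.
- **PA.** Under PA Parameters: "PA will be measured by an accelerometer as described for WP 1 at baseline and after 6 months". The WP 1 method is a 7-day wear period. A Polar watch also tracks PA during the intervention.
- **QoL, fatigue and PF.** Baseline and 6 months only. Attitude toward PA has one further measurement at 2 months.
- **Participants.** About 30 survivors aged 12 to 18 years from the lowest third of total PA in WP 1.
- **Analysis.** The Quantitative Data section for WP 4 is mainly descriptive. P values come from univariable and multivariable models with a random intercept for site, and are read as flags for trends rather than as tests.
- **Calendar.** In Results: "WP 4 recruitment was initiated in May 2021 and is still ongoing as of January 2022". By then 23 were included and 11 had completed. Completion was planned by July 2022.

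**The concern.** An effect is a contrast with what would have happened without the intervention. With one arm, the baseline value has to stand in for that counterfactual, which works only if nothing else would have changed over the interval. Two things plausibly would.

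**Season.** Each accelerometer measurement is one week in one season, and a gap of about 6 months tends to put the two weeks in opposite halves of the year, at sites in Norway, Finland and Germany. Within a child, season and before/after move together.

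**Growth.** Over 6 months many adolescents grow, which can raise isometric strength and absolute VO2peak. Unlike season, this does not change sign with the start month. It bears mainly on PF and much less on QoL, fatigue or attitude.

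A seasonal or growth change could be reported as an effect, or an autumn decline could hide a real gain. WP 4 is described as preparation for a large randomised trial, so a figure labelled as an effect is a natural candidate for planning it.

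**Working it through.** The plan derives no sample size, power or expected change for WP 4, so there is no figure to reproduce. The check is whether the stated design separates the intervention from season and growth, and how large the seasonal part could be.

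**1. Design features that could separate them.** The text has no concurrent control, no pre-intervention trend and no same-season repeat. A site random intercept absorbs differences in level between sites; it does not touch a change common to the children within a site. Reading P values as trend flags alters their interpretation, not what the mean change contains. WP 2 plans z scores for fitness outcomes where norms are available and records Tanner stage; neither is stated for WP 4.

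**2. Calendar.** The intervention lasts 6 months and 11 children had finished by January 2022, so those 11 started between May and about July 2021. Their PA change runs roughly from summer to winter. Completion by July 2022 implies last starts around January 2022, and those children run the other way.

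**3. Seasonal shift by start date (assumed shape).** Take season as a sinusoid of amplitude A peaking in mid-June. With t the start date in months from 1 January, the 6-month change without any intervention is −2A·cos(2π(t − 5.5)/12):

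- mid-June start: −2.0A
- mid-September start: 0
- mid-December start: +2.0A

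**4. Group mean under three start patterns.**

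- Starts spread evenly over May to January: 0.
- 11 starts evenly over May to July (average −1.80A) and 12 evenly over August to January (average +0.90A): (11 × −1.80 + 12 × 0.90)/23 = −0.39A.
- The same 23 plus 7 January starts (average +1.71A): (23 × −0.39 + 7 × 1.71)/30 = about +0.1A.

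The net shift can be small and can change sign, but nothing in the design makes it so.

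**5. Size in cpm.** The mean of 549 and SD of 180 are the general-population figures in the WP 1 power calculation. Assume a full summer-winter swing (2A) of 5% to 15%: 0.05 × 549 = 27 and 0.15 × 549 = 82 cpm. Assume a within-child correlation of 0.7.

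- SE of mean change, n=30: 180 × √(2 × (1 − 0.7)/30) = 25.5 cpm. At correlation 0.5 it is 32.9 cpm.
- Nearly all children starting at the same seasonal extreme: 27/25.5 = 1.1 SE to 82/25.5 = 3.2 SE.
- The −0.39A pattern: 0.39 × 13.5 = 5 cpm to 0.39 × 41 = 16 cpm. With n=23 the SE is 29.1 cpm, so this is 0.2 to 0.55 SE.
- The 11 early completers alone: 1.80 × 13.5 = 24 cpm to 1.80 × 41 = 74 cpm, downward.

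**6. False trend flags with zero intervention effect (n=30, two-sided 0.05, normal approximation, correlation 0.5 to 0.7).** A net shift of 5 cpm is flagged about 5% of the time, 16 cpm 8% to 10%, 27 cpm 13% to 19%, and 82 cpm 70% to 90%.

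**The case against.** The strongest reply is that this is a feasibility study. Most of its aims concern recruitment, adherence, safety and acceptability, its analysis is mainly descriptive, and it disclaims hypothesis testing. That limits the weight of the point. It does not make the effect aim answerable.

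Several stronger readings are tempting, and the document does not support them:

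- **That season is inseparable from time in the whole sample.** It is confounded within each child, but starts run over several months and the sign varies, so the group mean may partly cancel. The same spread is what makes a seasonal term possible at all.
- **That the visits are exactly 6 months apart.** The text says after 6 months and gives no window.
- **That the model adjusts for site and nothing else.** Multivariable models are allowed for and their covariates are left open, which an article may do. The lack of a named season or growth term is not itself the fault.
- **That a bias of 1 to 3 SE should be expected.** That range needs nearly all children to start in the same season.
- **That the WP 4 change will size the future trial.** No section says so. The risk lies in labelling the change an effect.

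A reader might also look to survivors remeasured in WP 2 as an untreated comparison. Their intervals vary from more than 3 months to possibly 1 to 2 years, and WP 2 ran in Norway and Switzerland rather than Norway, Finland and Germany. Choosing those in the lowest third on the same WP 1 value that serves as their baseline would build in regression to the mean. WP 4 lessens that problem by measuring PA afresh at its own baseline.

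The Polar tracking and the 2-month attitude measurement add within-arm detail but no counterfactual.

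**Conclusion.** The point stands as a mismatch between an aim and a design: WP 4 can describe change over about 6 months but cannot attribute it to the intervention. For PA the rival explanation is season, with a direction that depends on start month. The 11 children who had completed by January 2022 ran roughly from summer to winter, and later starters offset this only by chance. For raw strength and absolute VO2peak the rival is growth, which does not cancel across start months.

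The size of the net seasonal shift is unknown. It ranges from near 0 with balanced starts to about 1 to 3 SE if nearly all children start in the same season. These figures rest on an assumed swing of 27 to 82 cpm, a correlation of 0.7, n=30, and a general-population SD that may not describe the least active third. No figure is offered for growth, because the document gives no basis for one. The feasibility aims are unaffected. The aim should be reworded before WP 4 is reported.

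**What to change.** 1. Reword the aim as: *describe the within-child change in PA, attitude toward PA, QoL, fatigue and PF over 6 months*. State that this is not an estimate of the intervention effect and should not be used alone as the planning effect size for the future trial.
2. Report PA change by baseline season or month, with the distribution of start dates. Add a seasonal term if the starts are spread widely enough to support one.
3. Express fitness change as age- and sex-referenced z scores where norms exist, as WP 2 already plans. Where they do not, report raw change with a note that growth may contribute.
4. Do not use remeasured WP 2 survivors as a benchmark for the PA change.

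No new participants, visits or control arm are needed. The cost is a little extra analysis and a more modest conclusion. With about 30 children, the seasonal breakdown will be imprecise and should be presented descriptively.

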##### Intervention

The exercise intervention will last 6 months and starts with a personal motivational interview (MI) session at the baseline study visit. For each survivor, a central study coach is appointed who performs the MI and, together with the participant, defines a personal target of duration and intensity of PAs per week. The MI technique is a communication method that involves enhancing a patient’s internal motivation to change [75]. During this session, local structures (local coaches) will be identified that can help and support the survivor to reach their PA goals and maintain a more active lifestyle after the intervention. On the basis of this assessment, individualized PAs are defined and implemented into a survivor’s daily life. Each survivor will get a written personalized plan at the end of the session and a Polar watch (Polar Global) to track their behavior and provide immediate feedback on their achievements.

The central study coach will follow up with the survivor and local coaches with a phone call based on a predefined schedule of decreasing frequency over time (Table S1 in Multimedia Appendix 1). During the follow-up phone calls, the coach uses MI-inspired techniques and a standardized guideline to discuss adherence, motivation, progress, and possible problems. The training program can be adapted, and solutions for solving problems will be searched. The central coach will also follow the PA behavior in real time based on the Polar watch and set up an additional follow-up contact if the survivor struggles to reach his or her activity goals. The central coaches will be trained in the use of MI techniques to be used in the initial and follow-up conversations with survivors.

